### Relevant concomitant care permitted or prohibited during the trial {11d}

The physician will determine the use of diuretics, beta-blockers, ACEIs, ARBs, or ARNIs based on the condition of the patients, and other traditional Chinese medicines should be forbidden.

### Provisions for post-trial care {30}

Not applicable, as there is no anticipated harm or compensation required in lieu of trial participation.

### Outcomes {12}

#### Primary outcome

Cardiac function (from baseline to weeks 4, 12, and 24)
◦ Significant effects: cardiac function restored to level 1 or increased by level 2◦ Effective: heart function improved to level 1, but not to level 2◦ Invalid: no change in cardiac function◦ Deterioration: decrease in cardiac function by a single grade or more

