**Methods:**

A randomized, double-blinded, placebo-controlled clinical trial was proposed. A total of 122 patients with HFpEF will be randomly assigned to receive Zhigancao Tang granules or placebo for 12 weeks. The primary outcome measure is cardiac function. The secondary outcomes include measurement of the integral TCM syndrome score, echocardiography, 6-min walk test, N-terminal-pro hormone B-type natriuretic peptide level, atrial natriuretic peptide level, Minnesota Living with Heart Failure scale, and Lee’s scale. The outcome measures will be evaluated at baseline, 4 weeks, and 12 weeks. Adverse events will be evaluated from baseline till the 12-week follow-up period.

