### Sample size {14}

The sample size for this study was calculated based on the expected value of efficacy, according to the clinical trial results and analysis of data from previously published articles [13]. The total efficacy rates in the study and control groups were 93.3% and 73.3%, respectively. The significance level (alpha) was set at 0.05, and the statistical power was set at 80%. Based on our calculation, using the PASW statistical software (V.18.0), the experimental and control groups will each require a sample size of 51 patients. Considering a 20% loss to follow-up, 61 participants are required in each group. Therefore, this trial will require at least 122 participants in the current study.

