## Statistical methods

### Statistical methods for primary and secondary outcomes {20a}

Data analysis will be completed using the Statistical Packages of Social Sciences software (version 24.0). Qualitative indicators will be described in terms of frequency tables, percentages, or component ratios, whereas quantitative measures will be described in terms of mean, median, lower quartile (Q1), upper quartile (Q3), minimum, and maximum. For the comparative analysis of the two groups, the chi-square test, Fisher’s exact probability method, and Wilcoxon rank and inspection will be applied for qualitative data and *t* test will be applied for quantitative data, while the *t* test will be applied for quantitative data with normal distribution. Homogeneity test of variance will be conducted among the groups, with a cutoff level of 0.05, and the Satterthwaite method will be used to conduct the corrected *t* test when the variance is uneven. If the data do not follow normal distribution, the Wilcoxon rank test and inspection will be performed. The two-sided test will be uniformly used in the hypothesis test, and the test statistics and their corresponding *P* values will be provided, with *P* values ≤ 0.05 considered statistically significant and *P* values ≤ 0.01 considered highly statistically significant.

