## Trial status

The protocol version number and date were V1.0 and April 20, 2020, respectively. Patient recruitment has commenced in April 2019 and will end in April 2022.

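### The primary outcome is assessed at weeks 4, 12 and 24 with no deciding visit, while the sample size covers one two-level comparison at 5%.

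*Protocol article*

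**What the plan says.** - **Outcomes {12}, Primary outcome:** the primary outcome is "Cardiac function (from baseline to weeks 4, 12, and 24"), graded in four ordered categories from significant effect to deterioration. No visit is singled out. Table 4 schedules cardiac function at week 0 and at all three later visits.
- **Abstract, Methods:** "The outcome measures will be evaluated at baseline, 4 weeks, and 12 weeks". Week 24 is absent.
- **Plans for assessment and collection of outcomes {18a}:** treatment lasts 12 weeks and follow-up another 12, so week 24 is an off-treatment assessment.
- **Sample size {14}:** "The total efficacy rates in the study and control groups were 93.3% and 73.3%, respectively". With alpha 0.05 and 80% power, the result is 51 per group, raised to 61 for loss to follow-up, 122 in total. No time point is attached to the rates, and the article does not say which of the four categories make up total efficacy.
- **Statistical methods {20a}:** every test is two-sided, and one threshold serves them all, "with *P* values ≤ 0.05 considered statistically significant". No hierarchy of visits, adjustment, or rule requiring all visits to agree is given.
- **Inclusion criteria {10}:** patients in NYHA grades I to III may enter.

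**The concern.** A primary outcome needs one time point, or a rule for combining several. Here three visits stand side by side. Two fall within the treatment period and one falls 12 weeks after it, so they answer different questions: response on treatment, and persistence after it. If the visits disagree, the document does not say which result is the trial's answer. A positive finding at any one of them could be presented as the primary result.

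The link to the sample size is loose in the same way. The outcome has four levels and the calculation has two, with no stated mapping between them. Reaching level 1 appears in the wording of both of the top two categories, so the mapping cannot be read off safely. A patient who enters at NYHA grade I cannot improve by a class, and the categories do not say how such a patient is counted.

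**Working it through.** **Step 1: reproduce the stated sample size.** Inputs from Sample size {14}: p1 = 0.933, p2 = 0.733, alpha 0.05, power 80%. Two-sided testing comes from Statistical methods {20a}.

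n per group = (z_alpha + z_power)² × [p1(1 − p1) + p2(1 − p2)] / (p1 − p2)²

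- Variance term: 0.933 × 0.067 + 0.733 × 0.267 = 0.0625 + 0.1957 = 0.2582
- n = (1.960 + 0.842)² × 0.2582 / 0.2² = 50.7, rounded up to 51
- Power at 51: Φ(0.2 / √(0.2582/51) − 1.960) = Φ(0.851) = 80.2%

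The stated 51 is therefore one two-sided responder comparison at the full 5% level (unpooled variance). It contains no allowance for a second or third test. The pooled-variance formula gives 54, so the unpooled form is the one that matches.

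**Step 2: error rate if success at any of three visits counts.** Each visit is tested at |Z| ≥ 1.96 under no treatment effect. The between-visit correlation ρ of the test statistics is not in the document and is assumed.

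- Independent visits: 1 − 0.95³ = 1 − 0.8574 = 14.3%
- Equal correlation ρ, with c = 1.96: 1 − ∫ φ(u) [Φ((c − √ρ·u)/√(1 − ρ)) − Φ((−c − √ρ·u)/√(1 − ρ))]³ du

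| Assumed ρ | Chance of at least one P ≤ 0.05 |
|---|---|
| 0 | 14.3% |
| 0.5 | 12.5% |
| 0.7 | 10.9% |
| 0.8 | 9.8% |
| 0.9 | 8.4% |

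As ρ approaches 1 the figure falls towards 5%.

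**Step 3: what keeping all three visits as alternatives would cost.** With a Bonferroni level of 0.05/3 = 0.0167, z_alpha = 2.394.

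- n = (2.394 + 0.842)² × 0.2582 / 0.04 = 67.6, so 68 evaluable per group instead of 51
- Power with 51 evaluable: Φ(2.811 − 2.394) = Φ(0.417) = 66%

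Naming one visit keeps alpha at 0.05 and leaves the 51 evaluable per group unchanged.

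**The case against.** The strongest reply is that the article lists assessment visits, not confirmatory tests. Nowhere does it say that each visit is tested as primary or that one success is enough. If all three visits had to be positive, the error rate could not exceed 5%. This stands. A reader might infer that the plan as stated fails to control the 5% level, but the document supports only that the deciding visit is not fixed. The 8% to 14% applies to one reading that the text leaves open.

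A second reply is that a condensed article may leave detail to a statistical analysis plan. That is fair for methods but not for this core. The time point belongs to the outcome definition, which the article does give, and its abstract and outcomes section disagree. Lee's scale, a secondary outcome, has its response categories fixed at 12 weeks, so the primary outcome is less firmly defined than a secondary one.

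Several stronger readings are tempting and are not supported:

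- **Free choice of test.** The statement that "Wilcoxon rank and inspection will be applied for qualitative data", alongside chi-square and Fisher, is a general list for all categorical data. Assigning a test to each endpoint is commonly left to the analysis plan.
- **A larger error rate from the analysis at 60 patients.** The interim section states no test or threshold. That is a separate matter, and naming a primary visit would not resolve it.
- **A choice made after seeing results.** "The protocol version number and date were V1.0 and April 20, 2020, respectively", a year after recruitment began in April 2019. The dates are a separate question. Nothing shows that the outcome was chosen with knowledge of results by group, and the article states that blinding holds until the trial is completed.
- **Total efficacy means improvement by at least one NYHA class.** The sample size section does not define the term, and that definition would make every grade I entrant an automatic failure in both arms.

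**Conclusion.** The point holds in this form: the single primary outcome has three visits and no deciding one, the abstract omits one of the three, and the four categories are not mapped to the two-level rate used for sizing. That the sample size covers exactly one two-sided 5% comparison is reproduced arithmetically. The inflation to about 8% to 14% is conditional. It assumes that a positive result at any visit could be claimed, with equal between-visit correlation of 0.9 down to 0, neither of which the document states. It should be corrected before analysis, because without it there is no single primary answer when the visits differ. Confidence is high for the missing deciding visit, the mismatch with the abstract and the undefined responder mapping, and lower for the exact size of the error rate.

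**What to change.** - In Outcomes {12}, name week 12, the end of treatment, as the single primary time point and make weeks 4 and 24 secondary. Week 12 is also where Lee's scale is already classified.
- State that the primary analysis is the one responder comparison used in Sample size {14}, and attach the 12-week time point to the two rates there.
- Define which of the four categories count as effective, and state how patients who enter at NYHA grade I are handled in that definition.
- Make the four-category analysis secondary.
- Make the abstract, Outcomes {12} and Sample size {14} agree on visits and on the outcome.

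The cost is wording in the protocol, the registry entry and any analysis plan. No extra patients or visits are needed, and 51 evaluable per group stands as far as this point is concerned. Stratification by baseline NYHA grade is a separate design choice and is not required by this correction.

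### NYHA class I patients are eligible but cannot improve on the primary outcome, and a change from class II to class I fits two of its response categories

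*Protocol article*

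**What the plan says.** The inclusion criteria (Eligibility criteria {10}) accept NYHA grades I to III and describe NYHA as the classification of cardiac function. The Primary outcome section (Outcomes {12}) sorts patients into four categories by change in level:

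- The best category is worded "Significant effects: cardiac function restored to level 1 or increased by level 2", so a patient can qualify either by where he or she ends up or by how far he or she has moved.
- The second is worded "Effective: heart function improved to level 1, but not to level 2", which taken at face value describes an end point and not a size of change.
- The third, named Invalid, is for patients whose class stays the same.
- The fourth, named Deterioration, is for patients who worsen by at least one class.

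It sets no order of precedence between them, no separate rule for patients who start in class I, and no exclusion of those patients from the primary analysis.

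Sample size {14} rests on a responder proportion: "The total efficacy rates in the study and control groups were 93.3% and 73.3%, respectively". With alpha 0.05 and 80% power it arrives at 51 per group, and 61 per group after an allowance for loss to follow-up. What counts towards total efficacy is not defined.

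**The concern.** There are two separate problems.

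The first is a ceiling. A patient who enters in class I has no better class to move to. Remaining in class I is no change, hence Invalid; a lenient assessor might instead call it restored to level 1, hence Significant. Neither result says anything about the treatment. Such patients add fixed failures (or fixed successes) to both arms and shrink the difference that the trial was sized to detect.

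The second is that the categories do not divide the possible outcomes cleanly. At least one common improvement fits two categories, and on the literal wording another fits none. The Discussion already concedes that the outcome is subjective; unclear categories leave the assessor further discretion that could have been avoided.

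**Working it through.** **Inputs.** Eligible classes I to III (Inclusion criteria); the four category definitions (Primary outcome); 93.3% vs 73.3%, alpha 0.05, 80% power and 51 per group (Sample size {14}); two-sided testing, since "The two-sided test will be uniformly used in the hypothesis test" (Statistical methods {20a}). The class I share, f, is not given and is assumed below. The Primary outcome section does not name NYHA; reading level as NYHA class is an inference from the eligibility criteria.

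**The plan's own figure.** Normal approximation with unpooled variance:

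n = (1.960 + 0.842)² × (0.933 × 0.067 + 0.733 × 0.267) / 0.20² = 7.849 × 0.2582 / 0.04 = 50.7, so 51 per group. This reproduces the plan. Exact power of the two-sided chi-square test at 51 per arm is 80.0%.

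**Each change set against the categories.** The middle column takes the Effective line literally (improved *to* level 1). The right column reads it as improved *by* one level.

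| Change | Literal: to level 1 | Alternative: by one level |
|---|---|---|
| I to I | Invalid | Invalid |
| I to II or worse | Deterioration | Deterioration |
| II to I | Significant and Effective | Significant and Effective |
| II to II | Invalid | Invalid |
| II to III or worse | Deterioration | Deterioration |
| III to I | Significant and Effective | Significant |
| III to II | none | Effective |
| III to III | Invalid | Invalid |
| III to IV | Deterioration | Deterioration |

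The class I ceiling and the II-to-I overlap appear under both readings. The III-to-II gap and the III-to-I overlap appear only under the literal one. (The lenient option for I to I, restored to level 1, is left out of the table.)

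**Effect of the ceiling on the responder rate.** Suppose 93.3% and 73.3% hold among patients who can improve. With class I counted as failures, the rates become 0.933 × (1 − f) and 0.733 × (1 − f). No arm can exceed 1 − f, so 93.3% is out of reach once f is above 1 − 0.933 = 6.7%. With class I counted as successes, f is added to both rates. With class I left out, the rates are unchanged and the number per arm is 51 × (1 − f), rounded. Exact chi-square power, starting from 51 evaluable per arm:

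| f (assumed) | Rates, class I as failures | Power | Power, class I as successes | Power, class I left out (n per arm) |
|---|---|---|---|---|
| 0 | 93.3% vs 73.3% | 80% | 80% | 80% (51) |
| 5% | 88.6% vs 69.6% | 67% | 77% | 79% (48) |
| 10% | 84.0% vs 66.0% | 57% | 75% | 77% (46) |
| 20% | 74.6% vs 58.6% | 41% | 69% | 72% (41) |

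A pooled normal approximation gives similar values for the failure column: 78%, 66%, 56% and 40%.

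**The case against.** Much of the wording can be read charitably. The Significant line speaks of an increase by level 2 and the Deterioration line of a fall by a grade, so the Effective line may simply be a loose rendering of improvement by one level but not two. That is plausible. A reader might infer that a III-to-II change certainly has no category; the document supports this only on the literal wording.

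The overlap may also be harmless for sizing. If total efficacy means Significant plus Effective, a II-to-I patient is a responder either way. The overlap then matters only when the four categories are compared, and the statistical methods list chi-square, Fisher and Wilcoxon tests for qualitative data without tying one to this outcome. This stands.

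A reader might go on to conclude that many patients cannot be classified, or that the trial's real power is 57% or lower. Neither is shown. Class I patients can be classified; their difficulty is that they cannot respond. The baseline NYHA mix is not given, and entry requires a diagnosis that the Background describes as symptom-based plus a symptomatic TCM syndrome, which suggests that few will be in class I. That is an inference and not a limit, since the criteria admit class I explicitly and even a 5% share is costly if counted as failures. Nor is there a question of sites reading the wording differently: the trial has one centre, so any variation is between assessors or over time.

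None of this removes the ceiling or the II-to-I overlap.

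**Conclusion.** The point holds in this form: as written, class I patients are enrolled into a primary comparison in which they cannot improve, and a II-to-I change satisfies two categories on any reading. These follow from rules the article states, so they are not details left to an analysis plan.

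The ceiling bears on the responder rate used for sizing. The literal III-to-II gap would bear on it too, if that reading is the intended one. The II-to-I overlap bears only on a four-category comparison.

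The loss of power cannot be fixed at one number. It depends on the unknown class I share, on whether those patients are counted as failures or successes, and on the planning rates holding in classes II and III. The illustrative shares serve to show that a small one is enough to matter. Because this is the primary endpoint, it should be settled before any comparison by arm.

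**What to change.** 1. State that cardiac function is NYHA class, if that is what is meant.
2. Restrict the primary efficacy analysis to patients in NYHA class II or III at baseline. The subset is defined before randomisation, so the comparison remains a randomised one. Class I patients stay in the safety and secondary analyses.
3. Define the primary responder as improved by at least one class.
4. Make the four categories mutually exclusive and exhaustive, in one of two ways: by number of classes improved (two, one, none, worse); or by keeping restoration to level 1 as Significant, giving it stated precedence, and defining Effective as any other one-class improvement (III to II). The first moves II to I out of Significant, which is a real redefinition; the second keeps the existing criterion.

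**Cost.** This is more than a wording change. Fewer patients count towards the primary analysis, with power of about 77% or 72% if 10% or 20% are in class I, so the stated 80% should be restated for the class II–III number. Keeping 51 evaluable class II–III patients per arm would take 51/0.90 = 57 or 51/0.80 = 64 evaluable patients per arm in all. Because Interim analyses {21b} describes an analysis at 60 patients, the change should be dated and documented as made without knowledge of results by arm.

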#### Secondary outcomes

Echocardiography (from baseline to weeks 4 and 12): Echocardiographic measurement of LVEF, left ventricular end diastolic diameter (LVEDd), left ventricular end-systolic diameter (LVESD), ratio of left ventricular early diastolic fast filling peak to late diastolic filling peak (E/a), and ratio of early diastolic velocity of mitral valve to early diastolic annular velocity (E/e) [11].Lee’s scale (from baseline to weeks 4, 12, and 24)
◦ Significant effect: decrease in score by > 75% after 12 weeks◦ Effective: decrease in score by 50%–75% after 12 weeks◦ Invalid: decrease in score by < 50% after 12 weeks◦ Aggravation: score is unchanged or higher than the score recorded before the treatmentThe Minnesota Living with Heart Failure Questionnaire (MLHFQ) scale (from baseline to weeks 4, 12, and 24): The symptoms of heart failure substantially affect patients, and the MLHFQ scale is used worldwide to assess the quality of life in patients with heart failure [12]. The MLHFQ scale, consisting of 21 questions related to physical and emotional changes, will be used to assess the impact of heart failure on the quality of life in the last 4 weeks. Higher scores indicate worse outcomes. Patients will be assessed based on the scale before and after the trial.Six-minute walking test (from baseline to weeks 4, 12, and 24): This test is a measure of the greatest distance the patient can traverse by walking on a hard ground without obstacles within 6 min at the fastest possible speed. It provides a comprehensive assessment of the exercise capacity of the patient. The differences in the distance covered by the patients in each group will be observed before and after the treatment to evaluate their exercise endurance and quality of life.NT-proBNP, ANP (from baseline to weeks 4 and 12): NT-proBNP is a reliable and sensitive indicator of heart failure. Its elevation is positively correlated with the severity of heart failure. Changes in the levels of NT-proBNP and ANP in each group will be measured before and after treatment.Integral TCM syndrome score (from baseline to weeks 4 and 12; the scores and details are presented in Tables 2 and 3): A scale of 0–6 points and half quantitative points will be used to score the patients according to the severity of clinical symptoms.
◦ Significant effect: inhibition or complete suppression of primary and secondary clinical symptoms and reduction of syndrome score by ≥ 70%◦ Effective: significant improvement in clinical symptoms, and reduction of syndrome score by 30–70%◦ Ineffective: reduction of treatment syndrome score by < 30%◦ Aggravation: the score after treatment exceeds the score before treatment

**Table 2 Tab2:** Traditional Chinese medicine symptom score

	None	Mild	Moderate	Severe
Palpitation	0	2	4	6
Panting	0	2	4	6
Lassitude	0	2	4	6
Spontaneous sweating	0	2	4	6
Night sweating	0	2	4	6
Dizziness	0	2	4	6
Dry mouth	0	2	4	6
Vexation	0	2	4	6

**Table 3 Tab3:** Detailed description of symptoms according to traditional Chinese medicine

	None	Mild	Moderate	Severe
Palpitation	No symptom	Occasional occurrence; slight uncomfortable feeling	Regular occurrence; lasts for a long duration; intense uncomfortable feeling	Frequent occurrence; uncontrolled; considerable influence on the quality of life
Panting	No symptom	Slight and no influence on routine activities	Heavy, but can still manage to perform routine activities	Too heavy; cannot perform routine activities
Lassitude	No symptom	Slight and can work	Heavy, but can still manage to work	Too heavy; cannot work or continue routine activities
Spontaneous sweating	No symptom	Slight sweating after activities	Heavy sweating without any activity	Profuse sweating
Night sweating	No symptom	Occasional occurrence; sweating primarily in the head	Regular occurrence; sweating primarily on the chest and back	Frequent occurrence; sweating all over the body
Dizziness	No symptom	Slight, and no influence on work	Heavy, but can still manage to work	Too heavy; cannot work
Dry mouth	No symptom	Slight; no need to drink water	Severe; need to drink water occasionally	Intolerable; need to drink water frequently
Vexation	No symptom	Slight and occasional occurrence	Heavy and regular occurrence, but tolerable	Unbearable; severe impact on the quality of life

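### Results for the TCM syndrome score and Lee's scale are defined only as percentage-reduction bands, so low-power tests remain open, grades depend on baseline, and an unchanged Lee score can count as worse

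*Protocol article*

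**What the plan says.** The TCM syndrome score is numeric: "half quantitative points will be used to score the patients according to the severity of clinical symptoms". Table 2 of the protocol article lists eight symptoms, each scored 0, 2, 4 or 6. Secondary outcomes then defines four result bands:

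- top band: "reduction of syndrome score by ≥ 70" (per cent), together with suppression of symptoms;
- middle band: "Effective: significant improvement in clinical symptoms, and reduction of syndrome score by" 30-70%;
- "Ineffective: reduction of treatment syndrome score by < 30" (per cent);
- "Aggravation: the score after treatment exceeds the score before treatment".

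Lee's scale is treated in the same way. Its top band is "Significant effect: decrease in score by > 75% after 12 weeks", the next is 50-75%, and then comes "Invalid: decrease in score by < 50% after 12 weeks". The last band, *Aggravation*, takes any score that is the same as or above the pre-treatment score. No item list or range is given for Lee's scale.

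Statistical methods {20a} chooses tests by data type: "the chi-square test, Fisher’s exact probability method, and Wilcoxon rank and inspection will be applied for qualitative data". Quantitative data go to a t test, or to a Wilcoxon test if not normal. No outcome is named there.

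**The concern.** The bands are the only result definition given for these two scores, whereas MLHFQ, walking distance and the natriuretic peptides are described as scores, distances or levels. An analyst following the text could reasonably test the bands, and the listed methods include two (chi-square and Fisher) that ignore their order. That would discard information already collected on the outcomes behind the trial's stated aim of evaluating clinical symptoms.

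The bands have two further problems. A percentage of the patient's own baseline gives equal point gains different grades. On Lee's scale, a patient who has not changed can be reported as worse.

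**Working it through.** **Sample size used for the power check.** The documents give no mean, SD, effect or power for either score, so there is no stated power to reproduce. The group size does reproduce from Sample size {14}, with 93.3% vs 73.3%, two-sided 0.05, 80% power and unpooled variance:

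n = (1.960 + 0.842)² × [0.933 × 0.067 + 0.733 × 0.267] / 0.20² = 7.849 × 0.2582 / 0.04 = 50.7, so 51 per group.

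**Dependence on baseline (TCM score).** The maximum is 8 × 6 = 48. Reduction = fall / baseline.

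| Baseline | 6-point fall | 10-point fall |
|---|---|---|
| 12 | 50% (middle) | 83% (top) |
| 24 | 25% (*Ineffective*) | 42% (middle) |
| 36 | 16.7% (*Ineffective*) | 28% (*Ineffective*) |

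The labels show the percentage range only, since the two upper bands also carry a symptom condition.

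**Unchanged score.** A change of 0% satisfies *Invalid* on Lee's scale (below 50%) and also *Aggravation* (same or higher). On the TCM score, 0% is *Ineffective*, and *Aggravation* requires a score above baseline. The two scales therefore treat a stable patient differently. A smaller overlap is that a TCM reduction of exactly 70% fits both upper bands.

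**Power, main setting (all inputs assumed except n = 51 and two-sided 0.05).** Control mean reduction 20-50%; active 15 percentage points more; SD 25-35 points. TCM baseline mean 22, SD 6, on the 0-48 grid; Lee baseline mean 7, SD 2, on an assumed 0-14 grid. Simulated loss of power against an analysis of the score adjusted for baseline:

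- chi-square on four bands: roughly 18-26 points;
- chi-square on responder yes/no: roughly 10-35 points;
- rank test on four bands: about 2-6 points.

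The baseline-adjusted analysis was highest in every setting. An unadjusted t test on change was ahead of the four-band chi-square by about 5-20 points and of the responder split by about 2-21. Against the rank test on the bands, it ranged from about 4 points ahead to 11 behind.

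**Power, second setting (sensitivity).** The effect was sized for 80% power on a continuous measure: d = (1.960 + 0.842) × √(2/51) = 0.555 SD. TCM baseline mean 24, SD 6, 2,000 runs per row. Power in per cent:

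| Model | Adjusted score | Rank, 4 bands | Chi-square, 4 bands | Responder |
|---|---|---|---|---|
| Proportional, control 20%, SD 25 | 75.7 | 70.4 | 52.1 | 63.8 |
| Proportional, control 50%, SD 25 | 75.2 | 68.8 | 51.9 | 41.2 |
| Point change, control 6, SD 6 | 76.8 | 63.8 | 47.3 | 57.2 |
| Point change, control 10, SD 6 | 78.5 | 61.4 | 42.0 | 49.4 |

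In the first row the losses are 75.7 − 70.4 = 5.3 (rank), 75.7 − 52.1 = 23.6 (four-band chi-square) and 75.7 − 63.8 = 11.9 (responder). In the last row they are 78.5 − 61.4 = 17.1, 78.5 − 42.0 = 36.5 and 78.5 − 49.4 = 29.1. The rank test's loss is therefore small when treatment acts proportionally and larger when it shifts points.

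**The case against.** The strongest objection is that the plan does not say the bands will be tested. A reader might infer that both outcomes must go to the qualitative tests, but {20a} selects by data type and names no outcome. Both scales are also listed as measured at stated weeks, and the quantitative route is open to the raw totals. The choice may be settled in an analysis plan that is not shown. This stands: the criticism is of the only result definition given and of the tests it leaves open.

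A reader might also infer that banding carries a fixed cost in power. It does not. The loss depends on the test and on distributions the documents do not give. The Wilcoxon test is among the listed methods and suits ordered bands, and in some settings it beats an unadjusted t test on change. The responder split is also not defined for these scores. All of this stands, which is why the figures are conditional and the comparison is with a baseline-adjusted analysis. Lee's figures are illustrative only.

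Finally, any percentage measure depends on baseline, and preferring absolute change is partly a matter of taste. The middle TCM band also requires improved symptoms, so a 30% fall alone does not earn the label. Both points are fair, but neither removes the conflict over an unchanged Lee score.

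**Conclusion.** The point holds in a limited form. The text defines these two outcomes only as bands and does not exclude unordered tests on them. If such tests were used, the loss against a baseline-adjusted analysis of the score would be roughly 18-26 points (four-band chi-square) or 10-35 points (responder split) under the main assumptions. With a rank test on the bands it would be about 2-6 points, rising to about 17 if treatment shifts points instead of percentages.

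The baseline-dependent grading and the double classification of an unchanged Lee score follow from the text alone. The second can report stable patients as worse, contrary to the TCM score. Both scales are secondary and the sample size is not tied to either, so the primary conclusion is unaffected.

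**What to change.** In Secondary outcomes, name the total TCM syndrome score (0-48) and the total Lee score as the tested variables. Compare them between groups with adjustment for the baseline score, and report the difference with a 95% CI. Keep the four bands as descriptive tables, and place an unchanged Lee score in *Invalid* only.

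The cost is a wording change and one analysis line. The totals are already needed to compute the bands, so no data, visits or patients are added. The downside is that the band-based efficacy rate for these two scales becomes descriptive instead of tested.
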